#### 2.3.3 Rejection criteria

1. Patients with documented non-adherence to prescribed medication regimens, precluding reliable therapeutic effect assessment;2. Patients withdrawing from the trial during the study period through self-initiated or legal guardian-requested discontinuation;3. Patients using concomitant medications outside the approved trial protocol, particularly agents known to compromise trial integrity or confound efficacy assessments.

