#### 2.3.4 Corresponding treatment for dropout and loss to follow-up cases

1. Upon occurrence of serious adverse events requiring physician-directed trial discontinuation, such cases shall be classified as treatment failures;2. Disease progression during the trial period or emergence of confounding symptoms compromising outcome assessments, when leading to investigator-initiated termination, shall be categorized as therapeutic non-responders;3. Protocol deviations exceeding acceptable thresholds (e.g., medication adherence poor) precluding reliable efficacy evaluation shall be excluded;4. Cases where unblinding or emergency unblinding occurs during the trial.

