### 2.4 Sample size estimation, blind and randomization

Sample size determination was conducted using methodology derived from prior RCT, indicating a minimum requirement of 31 participants per group. This calculation yields a baseline enrollment target of 62 subjects. To account for potential attrition (anticipated dropout rate = 20%) and ensure adequate power for intent-to-treat analysis, the final adjusted sample size was established at 74 participants.

This randomized controlled trial will enroll 74 participants allocated through SAS-generated block randomization with 1:1 assignment to either the intervention or control arm. Opaque sequentially numbered envelopes containing allocation codes will be managed by a head nurse. The head nurse on duty distributes the envelopes to the attending physicians according to the order of subjects’ enrollment, and the attending physicians assign the treatment plans to the patients according to the group numbers. The head nurse on duty assigns a sequence number based on the attending physician’s diagnosis. A designated person from the project team is responsible for distributing the treatment medication to the subjects. A specific person within the research team enters the data, and a teacher from the statistical consulting room is responsible for data analysis. When the results are ready, a third party is present to jointly unblind the results. In accordance with the principles of blinding, neither the patients, the attending physicians, nor the data statisticians and analysts are aware of the specific group assignments.

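### Section 2.3.4 excludes randomised patients for deviations such as poor adherence, which contradicts the intent-to-treat analysis that Section 2.4 gives as the reason for 74 participants

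*Protocol article*

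**What the plan says.** Three sections of the protocol article bear on who is analysed.

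- **Section 2.4** (sample size) raises 62 participants to 74 for 20% dropout and to "ensure adequate power for intent-to-treat analysis". This is the only mention of intent-to-treat in the article.
- **Section 2.3.3** (rejection criteria), which is separate from the exclusion criteria of Section 2.3.2, lists three groups: "Patients with documented non-adherence to prescribed medication regimens, precluding reliable therapeutic effect assessment"; "Patients withdrawing from the trial during the study period through self-initiated or legal guardian-requested discontinuation"; and "Patients using concomitant medications outside the approved trial protocol, particularly agents known to compromise trial integrity or confound efficacy assessments". It does not spell out what rejection means for the analysis.
- **Section 2.3.4** (dropout and loss to follow-up) has four items. Item 1 covers patients taken off the trial for serious adverse events: "such cases shall be classified as treatment failures". Item 2 classes investigator-terminated progression as non-response. Item 3 is the explicit exclusion: "Protocol deviations exceeding acceptable thresholds (e.g., medication adherence poor) precluding reliable efficacy evaluation shall be excluded". Item 4 reads in full: "Cases where unblinding or emergency unblinding occurs during the trial". It has no verb and no consequence.

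Section 2.8 compares group means by independent t-tests and categorical data by χ² or rank tests, two-sided at 0.05.

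**The concern.** An intent-to-treat analysis keeps every randomised patient in the allocated arm. A rule that excludes patients because of what they did after randomisation produces a different analysis. The two statements cannot both be followed: an analysis plan that obeys Section 2.3.4 item 3 breaks Section 2.4, and one that obeys Section 2.4 breaks item 3.

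The removals may also be related to treatment. Section 2.5.1 has patients take 10 pills three times daily, that is 30 a day, for 12 weeks. Poor tolerability or lack of effect could lead a patient to miss doses, withdraw or use another medicine, and this could happen more in one arm than in the other. Item 3 refers to acceptable thresholds without giving one, so exclusion rests on a judgement made once treatment is under way. If the removed patients differ in prognosis between arms, the arms compared are no longer those that randomisation made comparable.

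Two smaller gaps sit beside this. The handling of unblinded cases is unfinished, and the labels for failure and non-response are not tied to any endpoint, although lung function and CAT would be compared as means.

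**Working it through.** **1. The text.** The contradiction needs no arithmetic, but the strength of the wording differs by group.

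| Group | Where | What is stated |
|---|---|---|
| Protocol deviations, e.g. poor adherence | 2.3.4 item 3 | Excluded, explicitly |
| Documented non-adherence | 2.3.3 | Rejected, by heading; agrees with item 3 |
| Withdrawal | 2.3.3 | Rejected, by heading only |
| Off-protocol medication | 2.3.3 | Rejected, by heading only |
| Unblinded cases | 2.3.4 item 4 | Nothing |
| Stopped for a serious adverse event | 2.3.4 item 1 | Labelled a failure, not excluded |
| Progression, stopped by the investigator | 2.3.4 item 2 | Labelled a non-responder, not excluded |

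Adherence to trial pills and withdrawal during the study can be observed only after randomisation. No section restricts the removals to a per-protocol set.

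**2. The plan's own sample size.** Inputs from Section 2.4: 31 per group, 62 in total, 20% dropout. 62 × 1.2 = 74.4, which reproduces 74, or 37 per arm. Division by the retained fraction would give 62 / 0.8 = 77.5, rounded up to 78.

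**3. What is left after removal.** 74 × 0.8 = 59.2, about 29.6 per arm. That is below the stated minimum of 62. With all 74 analysed as randomised there are 37 per arm. The article gives no power. If 31 per arm is assumed to give 80%, the detectable difference is (1.960 + 0.842) × √(2/31) = 0.71 SD. For that difference, 29.6 per arm gives 78% power and 37 per arm gives 86%.

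**4. Possible bias, on assumed values.** Assume no true effect, SD = 1 and 20% removed from each arm. In one arm the removed patients would have done m SD worse than those kept; in the other, removal is unrelated to outcome.

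- Mean of those kept minus mean of the full arm = 0.2 × m, which is 0.10 SD for m = 0.5 and 0.20 SD for m = 1.0.
- Standard error of the difference = √(2/29.6) = 0.26 SD.
- Two-sided rejection rate = P(Z > 1.96 − bias/SE) + P(Z < −1.96 − bias/SE), which is 6.7% and 12.0%.

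**5. Other scenarios.** Here the removed patients are m SD worse than their whole arm, so an arm with a fraction e removed is shifted by e × m / (1 − e). Each arm starts with 37, and the ranges run over m = 0.25 to 1.0.

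| Removed, arm A / arm B | Bias (SD) | Two-sided error |
|---|---|---|
| 20% / 20%, same m | 0 | 5.0% |
| 25% / 15% | 0.04 to 0.16 | 5.3 to 9.2% |
| 30% / 10% | 0.08 to 0.32 | 6.1 to 22.8% |

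Either arm could be the one favoured.

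**The case against.** The best case for the plan has several parts.

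- **Scope.** A reader might infer that non-adherent, withdrawn, off-protocol and unblinded patients are all removed. The text does not go that far. Exclusion is explicit only for deviations such as poor adherence. For withdrawal and other medication it is a reasonable inference from a heading. For unblinded cases it is not stated at all. It follows that items 1 and 4 of Section 2.3.4 cannot be shown to collide for a patient who has a serious adverse event and is unblinded; item 4 is simply incomplete.
- **Poor outcomes are partly kept.** Items 1 and 2 label patients stopped for serious adverse events or progression and do not exclude them. The route to bias is therefore narrower: non-adherence, self-withdrawal and other medication.
- **The labels can have a meaning.** Section 2.6.1.3 gives a 5-point CAT change and a TDI score of at least 1 as meaningful improvement, and Section 2.8 has tests for categorical data. The fair point is that no section connects the labels to an endpoint.
- **Blinding.** Section 2.4 keeps patients, physicians and analysts unaware of allocation, which limits arm-dependent decisions to exclude. It does not stop the pill's own effects, or the lack of them, from changing behaviour.
- **Condensed article.** Analysis sets are commonly defined in the analysis plan, and their absence from Section 2.8 is no fault.

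These points limit the claim, but they do not remove the contradiction. The article is not silent here: it states an exclusion rule that conflicts with the analysis it says it is powered for.

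**Conclusion.** The point holds in this limited form. Section 2.3.4 item 3, with the rejection criteria of Section 2.3.3 beside it, contradicts the intent-to-treat analysis named in Section 2.4. Item 4 is unfinished, and the failure and non-responder labels have no endpoint.

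The removals can bias the comparison. A reader might go further and infer that they will, or that a positive result could not be read as a treatment effect. The documents do not support that, because they give neither removal rates by arm nor the prognosis of those removed. The error of about 7 to 12% belongs to one assumed, asymmetric scenario; with equal removal and equal prognosis it stays at 5%. For scale, a bias of 0.10 to 0.20 SD is 14 to 28% of the 0.71 SD that 31 per arm could detect at an assumed 80% power.

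The fall to about 59 patients needs no assumption about prognosis, only that the 20% loss occurs as anticipated and that those patients are left out.

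The point matters because it leaves open who is analysed for efficacy in a trial of 37 per arm. It should be settled before unblinding, since choosing the analysis set afterwards would be open to influence from the results.

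**What to change.** 1. State that the primary efficacy analysis includes all randomised participants in their allocated arm, whatever their adherence, other medication or unblinding status.
2. Keep the outcome visits already scheduled in Table 2 for patients who are off trial medication and still consent to them.
3. Include patients who withdraw from the trial, using their data up to withdrawal, with a prespecified missing-data method. An example is a mixed model for repeated measures over the scheduled visits, with a sensitivity analysis for outcomes not missing at random.
4. Confine the removals in Section 2.3.3 and Section 2.3.4 item 3 to a supportive per-protocol analysis.
5. Complete item 4 of Section 2.3.4 so that it says how unblinded cases are handled in each analysis.
6. Apply the failure and non-responder labels only to a responder analysis, for example on the CAT or TDI cut-offs already stated in Section 2.6.1.3.

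The cost is protocol wording, a modest amount of extra analysis, and the effort of keeping scheduled visits for patients off treatment. The estimated effect may be somewhat smaller, because patients who did not take the pills as planned stay in the comparison.

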### 2.5 Intervention

#### 2.5.1 Composition, preparation, and administration of the trial medication

The treatment group received Yiqi Gubiao Pill (specific composition detailed in Table 1; each pill containing 0.19 g, prepared by the Department of TCM Preparation, Affiliated Hospital of Traditional Chinese Medicine, Xinjiang Medical University). Administration consisted of 10 pills orally three times daily after meals, continued for 12 weeks. The control group received a placebo matching Yiqi Gubiao Pill in appearance and core color (primary ingredients: starch and caramel; prepared by the TCM Preparation Room, Affiliated Traditional Chinese Medicine Hospital of Xinjiang Medical University). Participants were instructed to take 10 placebo pills orally three times daily after meals for 12 weeks (Figure 2).

**TABLE 1 T1:** The composition of Yiqi Gubiao Pill.

Chinese name	Latin name	Medicinal site
Dang-shen	Codonopsis radix	Root
Fu-xiao-mai	*Triticum aestivum*	Fruit
Bai-zhu	Atractylodes macrocephala Koidz	Rhizome
Ban-xia	Pinelliae rhizoma	Tuber
Chen-pi	Citri reticulatae pericarpium	Pericarp
Zi-su-zi	Perillae fructus	Fruit
Fu-ling	Poria cocos	Sclerotium
Yi-yi-ren	Coicis semen	Fruit
Fang-feng	Saposhnikoviae radix	Root
Kuan-dong-hua	Farfarae flos	Flower bud
Bei-mu	Fritillariae pallidiflorae bulbus	Bulblet
Huang-qin	Scutellariae radix	Root
Pi-pa-ye	Eriobotryae folium	Leafage

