#### 2.5.2 Conventional treatment

Both treatment and control groups receive standardized anti-tuberculosis therapy following the WHO-recommended RIPE regimen—an intensive 8-week phase with daily rifampicin, isoniazid, pyrazinamide, and ethambutol, followed by a 16-week continuation phase with rifampicin and isoniazid—and concurrently receive guideline-concordant COPD management, including maintenance bronchodilator therapy.

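### The rule that excludes randomised patients for poor adherence, read naturally, conflicts with the intent-to-treat analysis the trial is sized for

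*Protocol article*

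**What the plan says.** Section 2.3.4 of the protocol article assigns a status to patients who stop or deviate. For those stopped because of a serious adverse event, item 1 states that "such cases shall be classified as treatment failures". Those stopped by the investigator for progression or confounding symptoms "shall be categorized as therapeutic non-responders" under item 2. Item 3 is different: "Protocol deviations exceeding acceptable thresholds (e.g., medication adherence poor) precluding reliable efficacy evaluation shall be excluded".

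Section 2.3.3 (Rejection criteria) stands apart from the baseline exclusion list in section 2.3.2. Its item 1 covers "Patients with documented non-adherence to prescribed medication regimens, precluding reliable therapeutic effect assessment". Its item 3 covers "Patients using concomitant medications outside the approved trial protocol, particularly agents known to compromise trial integrity or confound efficacy assessments". Section 2.3.3 does not say what happens to a rejected patient's data.

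Section 2.4 enlarges the sample to 74 so as to "ensure adequate power for intent-to-treat analysis". This is the only analysis principle the article names. Section 2.8 names no analysis set.

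**The concern.** An intent-to-treat analysis compares patients as randomised, whatever their later adherence. A rule that drops patients for poor adherence selects on something that happens after randomisation and that treatment can influence. The retained groups are then no longer guaranteed to be comparable, and a difference between them may reflect who was removed as well as what the pill does. If section 2.3.4 item 3 were followed as written, the primary comparison would not be the one that section 2.4 says the sample was chosen to support.

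**Working it through.** **Does exclusion mean exclusion from the analysis?**

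1. It cannot be an eligibility rule. Baseline exclusions are in section 2.3.2, and adherence to a 12-week course is known only after randomisation.
2. The items before it each give an analysis status: failure (item 1) and non-responder (item 2). Item 3 gives exclusion where those items count the patient.
3. The reason stated in item 3 is that efficacy cannot be reliably evaluated, which is a reason about analysis. Section 2.3.3 item 1 gives almost the same reason for rejecting non-adherent patients.
4. Section 2.4 refers to intent-to-treat. Both statements can hold only if item 3 is confined to some other analysis set, and the article names none.

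**The plan's own figure.** Section 2.4 goes from 31 per group (62 in total) to 74 with 20% dropout: 62 × 1.20 = 74.4, which matches 74. Per arm, 74/2 = 37. Whether that is the right inflation is a separate matter, and nothing below depends on it.

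**Effect of removing patients.** In one arm of 37, let k be the number removed and g the mean of the removed minus the mean of the retained.

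- Full-arm mean = retained mean + (k/37) × g.
- Retained difference (treatment minus control) minus full difference = (kC × gC − kT × gT)/37, where C is control and T is treatment.
- One patient is 1/37 = 2.7% of an arm. With k = 1 and g = 5 CAT points (the meaningful change in section 2.6.1.3), that arm's mean moves by 5/37 = 0.14 points.
- The bias is zero only if kC × gC = kT × gT. Equal numbers removed are not enough if the gaps differ.

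**Illustration with assumed rates.** The article gives no rate of non-adherence or deviation, so these inputs are assumptions. Suppose there is no true effect, higher scores are better, and excluded patients average s below their arm's overall mean. With a fraction e removed, the retained mean rises by s × e/(1 − e).

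| Removed (one arm vs other) | s = 0.5 SD | s = 1.0 SD |
|---|---|---|
| 10% vs 10% | 0 | 0 |
| 20% vs 10% | 0.07 SD | 0.14 SD |
| 30% vs 10% | 0.16 SD | 0.32 SD |

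For example, 20% vs 10% with s = 1.0 gives 0.20/0.80 − 0.10/0.90 = 0.250 − 0.111 = 0.139 SD. The error favours whichever arm loses more of its poorly performing patients.

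**Is non-adherence plausible?** Section 2.5.1 states: "Administration consisted of 10 pills orally three times daily after meals, continued for 12 weeks". That is 10 × 3 = 30 pills a day for 84 days, or 2,520 pills, on top of anti-tuberculosis and COPD drugs. This shows burden. It gives neither a rate nor an imbalance between arms.

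**The case against.** The strongest reply is that item 3 does not say what the patients are excluded from. Analysis sets are commonly defined in a SAP, this is a condensed article, and a per-protocol definition in the full plan would remove the conflict. It is right that the absence of a per-protocol definition is no fault in itself, and that the natural reading is not the only possible one. But the point concerns a rule that is stated, set beside a principle that is stated. Followed as written, the rule contradicts the principle unless another document confines it.

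A second reply is that section 2.4 keeps patients, attending physicians and analysts blinded, and that serious adverse events and progression are retained as failures or non-responders. Both facts lower the risk: blinding guards against deliberate selection by arm. Neither prevents adherence itself from differing between arms.

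Three stronger readings are tempting and should not be made.

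- A reader might infer that patients on off-protocol medication are also excluded from analysis. Section 2.3.3 item 3 lists them under rejection without stating a consequence. The same problem arises only if rejection means removal from analysis.
- A reader might infer from section 2.6.3 that side effects of the pill interrupt dosing, that those patients are then removed as non-adherent, and that the pill is flattered. The pause is directed by the protocol, and nothing says it counts as poor adherence. This route is hypothetical, and the bias could run the other way.
- A reader might infer that treating a COPD exacerbation leads to rejection. Under section 2.5.2 both arms "concurrently receive guideline-concordant COPD management, including maintenance bronchodilator therapy", so guideline treatment is protocol care on the plain reading.

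**Conclusion.** The point holds for poor adherence and similar protocol deviations under section 2.3.4 item 3, supported by the parallel wording of section 2.3.3 item 1. It holds conditionally for off-protocol medication. It rests on reading exclusion as removal from the efficacy analysis, which the structure of section 2.3.4 favours but does not state outright; confidence is therefore medium.

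Neither the size nor the direction of any bias can be derived from the article. The effect of one removed patient is small (0.14 CAT points for a 5-point gap). The range up to 0.32 SD depends wholly on the assumed removal rates and gaps. Material harm is therefore possible but not shown. The wording should be corrected because the conflict is in the text and the remedy is cheap.

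**What to change.** State in sections 2.3.3 and 2.3.4 that non-adherence, off-protocol medication and protocol deviations are recorded, but neither end follow-up nor remove a randomised patient from the primary intent-to-treat analysis. Apply section 2.3.3 items 1 and 3 and section 2.3.4 item 3 only to a per-protocol sensitivity analysis. Withdrawal by the patient (section 2.3.3 item 2) is not at issue here, and section 2.5.2 needs no change.

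The cost is protocol wording. Table 2 already schedules the visits at which these patients would be followed, so no extra patients or procedures are needed. The downside is some dilution of the contrast between arms, of a size the article does not allow one to estimate. An intent-to-treat analysis accepts that dilution.

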### 2.4 Sample size estimation, blind and randomization

Sample size determination was conducted using methodology derived from prior RCT, indicating a minimum requirement of 31 participants per group. This calculation yields a baseline enrollment target of 62 subjects. To account for potential attrition (anticipated dropout rate = 20%) and ensure adequate power for intent-to-treat analysis, the final adjusted sample size was established at 74 participants.

This randomized controlled trial will enroll 74 participants allocated through SAS-generated block randomization with 1:1 assignment to either the intervention or control arm. Opaque sequentially numbered envelopes containing allocation codes will be managed by a head nurse. The head nurse on duty distributes the envelopes to the attending physicians according to the order of subjects’ enrollment, and the attending physicians assign the treatment plans to the patients according to the group numbers. The head nurse on duty assigns a sequence number based on the attending physician’s diagnosis. A designated person from the project team is responsible for distributing the treatment medication to the subjects. A specific person within the research team enters the data, and a teacher from the statistical consulting room is responsible for data analysis. When the results are ready, a third party is present to jointly unblind the results. In accordance with the principles of blinding, neither the patients, the attending physicians, nor the data statisticians and analysts are aware of the specific group assignments.

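### The target of 74 does not keep the protocol's minimum of 31 per group at its own 20% dropout rate; 78 would be needed

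*Protocol article*

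**What the plan says.** The whole calculation is in Section 2.4 of the protocol article. It takes a size from an earlier trial, "indicating a minimum requirement of 31 participants per group", and doubles it: "This calculation yields a baseline enrollment target of 62 subjects". It then adjusts for loss: "anticipated dropout rate = 20%) and ensure adequate power for intent-to-treat analysis, the final adjusted sample size was established at 74 participants". The next paragraph repeats 74 and specifies "block randomization with 1:1 assignment to either the intervention or control arm", which makes 37 per group.

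The inflation formula is not written out. No effect size, standard deviation, power or endpoint is given for the 31.

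Section 2.3.3 bears on what dropout does to the analysed numbers. Its rejection criteria include this item: "Patients withdrawing from the trial during the study period through self-initiated or legal guardian-requested discontinuation".

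**The concern.** An allowance for dropout should leave the required number after the expected loss. The loss applies to everyone randomised, so the required number is divided by the retained fraction. Adding 20% to the required number is a different operation and always gives too few, because 20% of the larger total is more than 20% of the smaller one. The step from 62 to 74 looks like that addition.

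If so, the trial plans for a loss that its target cannot absorb. Section 2.4 calls 31 per group the minimum and presents 74 as the number that protects it. A reader who relies on that sentence would believe 20% attrition is covered when it is not.

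**Working it through.** **Inputs, all from Section 2.4:** minimum 31 per group; 62 in total; dropout 20%; final size 74; allocation 1:1, so 37 per group.

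**Reproducing the stated figure**
- In total: 62 × (1 + 0.20) = 74.4, rounded down to 74.
- Per group: 31 × 1.20 = 37.2, rounded down to 37, and 2 × 37 = 74.
- Both routes give 74. They are inferred, since the article prints no formula.

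**Standard inflation**
- In total: 62 / (1 − 0.20) = 77.5, rounded up to 78.
- Per group: 31 / 0.80 = 38.75, rounded up to 39, and 2 × 39 = 78.
- Shortfall: 78 − 74 = 4 participants.

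**What each target leaves after 20% loss**

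| Randomised | Left in total | Left per group | Meets 31 per group? |
|---|---|---|---|
| 74 | 74 × 0.8 = 59.2 | 37 × 0.8 = 29.6 | No |
| 78 | 78 × 0.8 = 62.4 | 39 × 0.8 = 31.2 | Yes |

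In whole participants, 20% of 37 is 7.4. Losing 7 leaves 30 and losing 8 leaves 29; both are below 31.

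**Attrition that 74 can absorb**
- 1 − 62/74 = 12/74 = 16.2%, which is 6 of 37 per group.

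**Effect on power.** This part rests on assumptions, because the document states neither power nor effect size. Take a two-sided comparison of two means at α = 0.05 (the level in Section 2.8), and suppose that 31 per group was chosen to give a stated power. By the normal approximation, the standardised difference is d = (1.960 + z for that power) × √(2/31), and the power at n per group is Φ(d × √(n/2) − 1.960).

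| Assumed power at 31 per group | d | Power at 29.6 | Power at 37 |
|---|---|---|---|
| 80% | 0.712 | 78.2% | 86.4% |
| 90% | 0.823 | 88.6% | 94.3% |

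The loss from falling to 29.6 per group is between 1 and 2 percentage points. The last column shows the power if nobody were lost.

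**The case against.** The strongest reply is that the same sentence says the size is meant to "ensure adequate power for intent-to-treat analysis". If every randomised participant contributed an outcome, 37 per group would exceed 31 and power would be higher than planned. Section 2.3.4 also counts some discontinuations as treatment failures or non-responders, so not every dropout need leave the analysis.

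This does not rescue the figure:
- If all randomised participants supplied data, no allowance would be needed. Making one treats 31 as the number left after loss.
- Section 2.3.3 rejects participants who withdraw, and Section 2.3.4 excludes those whose poor adherence prevents an efficacy evaluation.
- The long-term decline analysis in Section 2.6.1.2, one of the primary endpoints, requires at least three valid lung function tests over 12 months. Participants lost early cannot enter it.
- A failure label supplies no value for the t-tests on continuous outcomes in Section 2.8.

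Three further points on the other side stand. The multiplication by 1.2 is inferred, though the shortfall is the same whatever formula was used. The practical effect is small, well within the uncertainty of any assumed effect size or dropout rate. And because the document names no target power, what is shown is a shortfall against its own minimum of 31, not a failure to reach a particular power.

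**Conclusion.** The concern holds. From the printed numbers alone, 74 participants with 20% dropout leave 59.2 (29.6 per group) against a stated minimum of 62 (31 per group). The size that meets the stated aim in expectation is 78, and 74 covers at most 16.2% attrition. This needs only the usual reading of a dropout rate as a share of those randomised. No fuller protocol or analysis plan could make these four figures agree.

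The size is modest: 4 participants at enrolment, or 1.4 per group after loss. The power cost of 1 to 2 points depends on the assumption that 31 per group was set for 80% or 90% power. No analysis method or safety provision is affected, but the sample-size justification is incorrect as written.

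**What to change.** Correct the sentence in Section 2.4 in one of two ways, and print the formula.

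1. **Keep the 20% allowance:** state 62 / 0.8 = 77.5, rounded up to 78, or 39 per group. This costs four more participants.
2. **Keep 74:** state that 37 per group retains the minimum of 31 only up to about 16% dropout, and that at 20% about 29 to 30 per group would remain, with correspondingly lower power. This costs one sentence and a slightly less favourable statement, with no extra recruitment.

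Whichever is chosen, carry the same number into the following paragraph, where 74 is repeated.

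### Section 2.4 has attending physicians receive the allocation envelopes and act on group numbers, which conflicts with their stated blinding unless the codes are masked, and the text does not say they are

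*Protocol article*

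**What the plan says.** Everything at issue stands in one paragraph of Section 2.4 of the protocol article.

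- Method: 74 participants are "allocated through SAS-generated block randomization with 1:1 assignment to either the intervention or control arm". No block size is given.
- Custody: "Opaque sequentially numbered envelopes containing allocation codes will be managed by a head nurse".
- Hand-over: "The head nurse on duty distributes the envelopes to the attending physicians according to the order of subjects’ enrollment".
- Use of the code: "the attending physicians assign the treatment plans to the patients according to the group numbers".
- Numbering: "The head nurse on duty assigns a sequence number based on the attending physician’s diagnosis".
- Dispensing: a designated member of the project team gives out the medication. Whether this person is blinded is not stated.
- Blinding: "neither the patients, the attending physicians, nor the data statisticians and analysts are aware of the specific group assignments". A third party attends a joint unblinding when the results are ready.

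Three other places bear on this. Section 2.5.1 describes a placebo matched in appearance and core colour, with the same pill count and schedule. Section 2.5.2 gives both arms the same anti-tuberculosis and COPD treatment. Emergency unblinding is foreseen in Section 2.3.4 (item 4) and in Section 2.6.3, which places the procedures in the DSMB charter.

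**The concern.** In a double-blind trial with a matched placebo, the treating physician needs only a pack number. Here the physician is given the allocation code and acts on a group number, and is then said not to know the group. The paragraph does not say what the envelope shows, who opens it, or whether the code belongs to one patient or to a whole arm.

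The outcomes make blinding important. CAT, mMRC and TDI are among the primary endpoints, the secondary outcome is a symptom score, and spirometry depends on effort. Several decisions also rest on someone's judgement: discontinuation after a serious adverse event, termination for progression or confounding symptoms, exclusion for poor adherence, and whether an adverse event is related to the study medication. Anyone who makes these calls or collects these outcomes with access to the group codes could be influenced by them. Lost concealment or blinding cannot be repaired in the analysis.

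The numbering sentence raises a second, smaller question. A sequence number that depends on a diagnosis does not fit pre-numbered envelopes issued strictly in order of enrolment.

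**Working it through.** The plan gives no figure to reproduce, so the main check is a comparison of statements.

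**Step 1. What can a group number decide?**
- Background treatment is the same in both arms (2.5.2).
- Pill count, schedule and appearance are the same (2.5.1).
- What remains is active pill versus placebo, so a treatment plan chosen by group number is the allocation itself.

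**Step 2. Can both statements about the physician be true?**
- If the group number is readable as active or placebo: no.
- If it is a masked label shared by an arm (say 1 or 2): yes in the narrow sense that the meaning is unknown, but the physician sees which patients share an arm.
- If it is unique to each patient: yes, without that problem. But the text speaks of group numbers, and a unique number would not be one.

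**Step 3. What would a masked two-level label still disclose?**

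*Linked unblinding.* Let k be the number of patients whose label a person knows. One code break identifies the meaning of both labels and so decodes all k. With unique numbers it decodes 1. The ceiling is k = 74, reached only if all 74 are enrolled and one person knows every label. Section 2.4 refers to several attending physicians, so k for any one of them may be well below that.

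*Predictability in 1:1 blocks.* Assume that the block size b and all earlier labels are known. With a and c assignments of the two labels left in the block, the best guess is right with probability max(a, c)/(a + c). Averaging over all orderings of the block:

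- b = 2: (1/2 + 1)/2 = 0.75.
- b = 4: position 1 gives 1/2. Position 2 gives 2/3. Position 3 gives (1/3)(1) + (2/3)(1/2) = 2/3. Position 4 gives 1. The mean is 2.833/4 = 0.708.
- b = 6 and b = 8, by the same enumeration: 0.683 and 0.666.

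| Assumed block size | Next label guessed correctly | Next label known with certainty |
|---|---|---|
| 2 | 75% | 50% |
| 4 | 71% | 33% |
| 6 | 68% | 25% |
| 8 | 67% | 20% |
| Concealed | 50% | 0% |

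These rates concern the label. They predict the treatment only for someone who also knows or suspects what the label means, for example after a code break.

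**Step 4. Enrolment order against diagnosis.** Envelopes are issued "according to the order of subjects" and their enrolment, while the head nurse "assigns a sequence number based on the attending physician" and the diagnosis made. If diagnosis here means confirmed eligibility, the two agree: each eligible patient takes the next number. If it means that the kind of diagnosis determines the number, they conflict. The text does not settle which is meant.

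**The case against.** The strongest reply is that the paragraph is clumsy but describes masked codes. It speaks of codes, says the physicians do not know the specific assignments, has a separate person dispense, and ends with a joint unblinding. The placebo is matched. How codes are built and packs labelled is detail that a journal article may leave to the full protocol, and emergency unblinding is referred to a charter that is not shown.

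Much of this stands. Masking is plausible, so the article does not show that physicians know the treatment. It does not dispose of the point, because the article states a procedure rather than leaving one out. That procedure puts a group number in the physician's hands, and a masked group number still links patients by arm.

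Three stronger readings are tempting, and the documents do not support them:

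- **That the attending physician judges causality, progression and termination.** Section 2.6.3 gives causality to researchers, and Section 2.3.4 describes termination for progression as initiated by the investigator. Only discontinuation after a serious adverse event is directed by a physician. The roles may overlap, but this is not stated. No section names the attending physician as outcome assessor either.
- **That one unblinding exposes all 74 allocations.** This is a conditional worst case (Step 3), not a property of the plan.
- **That the diagnosis sentence permits selective allocation.** Diagnosis is the gateway to the trial, the nurse assigns the number, and nothing says that a number can be chosen or skipped.

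**Conclusion.** The concern holds in this form: the paragraph has attending physicians both acting on group numbers and unaware of group assignments. Because the arms differ only in active pill versus matched placebo, the two statements conflict unless the codes are masked, and the article does not say that they are. Masking alone would not be enough if a two-level label is visible to physicians. It would show which patients share an arm, raise the predictability of the next label from 50% to 67–75% (assuming blocks of 8 down to 2, known block size and all earlier labels known), and let one emergency unblinding decode every other patient whose label is known.

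The diagnosis sentence is a secondary wording conflict that may mean no more than confirmed eligibility. The effect on the treatment estimate cannot be quantified from the document. The case for changing the text rests on the dependence of the double-blind claim on this paragraph and on the low cost of putting it right.

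**What to change.** 1. Remove the step in which physicians receive envelopes and act on group numbers.
2. Have the pill preparation room label each patient's supply with a unique sequential randomisation number and no group code.
3. Once eligibility is confirmed, the head nurse issues the next number strictly in enrolment order, and the designated dispenser hands out the pack bearing it. State that the dispenser sees no group code.
4. Reword the diagnosis sentence to say that a number is issued only after eligibility is confirmed.
5. Keep the randomisation list with the preparation room and an independent code-holder. The preparation room alone is not enough, because both the final and any emergency unblinding need access to the code. Provide code breaks for single patients, consistent with the emergency unblinding procedures that Section 2.6.3 refers to the DSMB charter.

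The cost is pack labelling, naming a code-holder and revising one paragraph. The preparation room, nurse and dispenser are already in the plan. Sample size, treatment and outcome schedule are unaffected.
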